### Description of interventions and distribution of supplementary foods

After collecting baseline information, each child in the intervention group will be given local ingredient-based supplement of 100 g with 20 g of sugar. The ration will be distributed on a daily basis for 12 weeks. The LIBS is made from 30 g of pumpkin seed, 25 g of peanut grain, 20 g of amaranth grain, 15 g of flaxseed, 10 g of emmer wheat, 25.2 g of sugar and 8 ml of oil. This supplement yielded 698.5 kcal (22.6 g protein, 40.89 g fat and 60.05 g carbohydrate). Similarly, each child in the control group will be given the conventional supplement (CSB+) with the amount of 150 g flour/day with 16 ml of oil (763.98.4 kcal, 23.5 g protein and 25 g fat) on a daily basis for a period of 12 weeks. The subjects will be served with both supplements in the morning as a breakfast (Table 1).

**Table 1 Tab1:** Nutrient composition of the supplementary foods

Nutrient	100 g of LIBS with 25.2 g of sugar plus 8 ml oil	150 g of CSB+ with 16 ml of oil
Energy (kcl)	698.5	763.98
Protein (gm)	22.6	20.25
Fat (gm)	40.89	30.76
Iron (mg)	8.1	6
Zn (mg)	5.6	7.5
Calcium (mg)	100	195
Phosphorous (mg)	470.55	300
Potassium (mg)	666.14	600
Magnesium (mg)	394.7	107.75
Sodium (mg)	84.6	41.25
Folic acid (μg)	49.4	90

Note: Nutrient values for the LIBS ration were calculated by using the USDA food composition database and NutriSurvey software. Nutrient values for the CSB+ was adapted from Amegovu KA, Ogwok P, Ochola S, Yiga P, Musalima HJ, Mutenyo E. Formulation of sorghum-peanut blend using linear programming for treatment of moderate acute malnutrition in Uganda. J Food Chem and Nutr. 2013; 1(2):67–77

Abbreviations: *LIBS* Local ingredients based supplement, *USDA* United States Department of Agriculture and *CSB+* Corn soy blend plus

According to the guidelines for selective feeding, all children 6–59 months of age will receive the same amount of food [23]. During the intervention period, the food distributers will visit households daily to assist the caregivers in the preparation of porridge and feeding, to advise, assess and resolve difficulties with feeding. Besides, they will check for and quantify the amount of supplement consumed by the children.

### Data quality management

Scheduled as well as unscheduled home visits and close follow-up to check feeding procedure will be made by the supervisors and investigator. If the child is a twin, an additional amount of supplementary food will be given to the caregiver to confirm that the enrolled child is provided with a full portion.

If two children with MAM are found in the same household, both children will receive food but only the randomly selected child will be enrolled in the study. If the recruited child is not at home during the time of follow-up, data collectors will revisit those households until they find the child. Sessions for standardization of anthropometric measurements will be carried out on a monthly basis. Monitoring of the food distribution process, feeding techniques and use of the provided food supplements will be carried out among randomly selected households on a twice-monthly basis. After data collection, the filled questionnaires will be stored in a secured place, and data entry will start. Double data entry and checking for consistencies will be carried out.

### Data analysis

All data collection sheets will be controlled by the field supervisors for completeness. EpiData version 3.1 will be used for all data entry. Two data clerks will enter data simultaneously to ensure data quality. Continuous data quality evaluation will be made through automatic consistency checks. Statistical significance is set at 5% for all analyses. Statistical analysis will be done using SPSS and STATA software for survival and hazard ratio. The probability of recovery rate will be predicted in Kaplan-Meier (log rank) curves of survival analysis. T-tests, analysis of variance (ANOVAs) and chi-square tests will be used to assess baseline characteristics. In accordance with recommendations for analyzing and reporting equivalence and non-inferiority trials, both intention-to-treat (ITT) and per protocol (PP) analyses will be done, and the 95% CI will be used to infer whichever variances are significant [24]. The ITT analyses will include all children enrolled in the study whereas the PP analyses will exclude children who lost to follow-up, refused and transferred out of the management programme but include children discharged as cured, died or non-cured.

Logistic regression will be used to test for interactions between the recovery rate and other variables. Mean recovery time and median recovery time, mean differences of MUAC and mean difference between WHZ scores will be computed to describe the magnitude of the difference between the two groups.

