### Hypothesis

In MAM children aged 6 to 59 months, intervention with LIBS will, within 12 weeks (with a 7% margin of non-inferiority), will not have an inferior recovery rate as children with MAM receiving CSB+.

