### Sample size calculation

The proportion of children who recover from MAM in an area where there is a supplementary feeding program (CSB+) is about 67% [12]. The sample size assumes that the expected percentage response in an experimental group is 60% and in a control group is 67%, with the non-inferiority criterion set to be an absolute value of 7%. To achieve 80% power to demonstrate non-inferiority, it is estimated that 162 subjects per group would be required, including a 10% withdrawal rate. This leads to a total required sample size of 324 subjects. The anticipated 10% dropout rate was used based on the observed dropout rate reported in two studies [12, 13]. For this sample size calculation, the PharmaSchool sample size calculator for non-inferiority trials was used.

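### The 80% power stated for 162 children per arm does not belong to the planned 95% CI analysis: 162 fits only a one-sided 5% test with the expected difference reversed

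*Protocol article*

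**What the plan says.** The Sample size calculation section assumes that "the expected percentage response in an experimental group is 60% and in a control group is 67" per cent, "with the non-inferiority criterion set to be an absolute value of 7" percentage points. It continues: "To achieve 80% power to demonstrate non-inferiority, it is estimated that 162 subjects per group would be required, including a 10% withdrawal rate". On method it says only that "the PharmaSchool sample size calculator for non-inferiority trials was used". It states no alpha, no sidedness and no formula.

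The Data analysis section says "Statistical significance is set at 5% for all analyses", again without sidedness. In the sentence that plans intention-to-treat and per-protocol analyses in line with non-inferiority reporting recommendations, it says "the 95% CI will be used to infer whichever variances are significant". I read "variances" there as differences between the arms. No one-sided 5% test and no 90% interval appears anywhere in the article.

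**The concern.** Non-inferiority is a one-sided question. Comparing the lower limit of a two-sided 95% CI with the margin is a one-sided 2.5% test. If the sample size was computed at one-sided 5%, the 80% power describes a more lenient test than the one the Data analysis section plans. Because the alpha is not printed, a reader cannot see this without working back from the result. At stake is whether the sponsor, ethics committee and readers know how likely the trial is to succeed under its own decision rule, and how to read a failure to show non-inferiority.

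**Working it through.** **Inputs** (Sample size calculation section): recovery 60% on LIBS and 67% on CSB+, margin 7 points, power 80%, withdrawal 10%, stated result 162 per arm. Allocation is 1:1 (recruitment and randomization section).

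**Formula** (unpooled variance): n per arm = (z for 1-alpha + z for power)² × [p1(1-p1) + p2(1-p2)] / distance². The distance is the margin minus the assumed deficit of LIBS. Dividing by 0.9 allows for withdrawal.

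Variance term at 60% and 67%: 0.60×0.40 + 0.67×0.33 = 0.2400 + 0.2211 = 0.4611.

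**Step 1: reproduce 162.**
- As written, LIBS is 7 points worse and the margin is 7 points. The distance is 0.07 - 0.07 = 0, so no finite n exists.
- With the difference reversed, the distance is 0.07 + 0.07 = 0.14. At one-sided 5%: (1.645 + 0.842)² × 0.4611 / 0.0196 = 145.45. Then 145.45/0.9 = 161.6, which rounds up to **162**. Rounding to 146 before dividing gives 163.
- Solving back from 162×0.9 = 145.8 evaluable gives alpha = 0.0497.

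**Step 2: variants at 80% power that do not give 162.**
- Distance 0.14, one-sided 2.5%: (1.960 + 0.842)² × 0.4611 / 0.0196 = 184.65, so 185 evaluable; 184.65/0.9 = 205.2, so **206** per arm (412 in total, against 324).
- Distance 0.14, one-sided 10%: 106.05; 106.05/0.9 = 117.8.
- Equal 67% rates, distance 0.07: 558 evaluable (620 per arm) at one-sided 5%; 709 evaluable (788 per arm) at one-sided 2.5%.
- Ordinary superiority comparison of 67% with 60%: 742 per arm (two-sided 5%) or 584 (one-sided 5%), before withdrawal.

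**Step 3: power with 146 evaluable per arm.** Power = Φ(distance/SE - z for 1-alpha), with SE = √(variance term/146). For 60%/67%, SE = √(0.4611/146) = 0.0562. For 67%/67%, SE = √(0.4422/146) = 0.0550.

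| True rates (LIBS / CSB+) | Distance | One-sided 5% | Two-sided 95% CI (one-sided 2.5%) |
|---|---|---|---|
| 67% / 60% (reversed; reproduces 162) | 0.14 | 80.1% | 70.2% |
| 67% / 67% | 0.07 | 35.5% | 24.6% |
| 60% / 67% (as written) | 0 | 5% | 2.5% |

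If all 162 per arm are analysed, the last column becomes 74.7%, 26.8% and 2.5%, so the denominator does not rescue the 80%.

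**The case against.** The strongest reply is that the article writes only one inference rule for non-inferiority, the 95% CI, and that an unqualified 5% level is ordinarily two-sided and then agrees with it. That stands.

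A reader might infer that the protocol offers two rival decision rules, so that the type I error is 2.5% or 5% depending on the sentence followed, with the choice open until the data are seen. The two levels would indeed disagree near the boundary. With 98 of 146 recovered on CSB+, 101 to 103 recovered on LIBS gives 90% CI lower limits of -6.9 to -5.5 points (pass) and 95% CI lower limits of -8.6 to -7.2 points (fail). But the documents do not support that reading, because no sentence permits a one-sided 5% decision or a 90% interval. Sizing a trial at a looser alpha and analysing it at a stricter one lowers power; it does not raise the false-positive rate.

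Two further points against the concern also stand. The one-sided 5% alpha is inferred, not stated, though the match is exact. And the reproduction depends on reversing the assumed difference, a separate and larger fault: correcting alpha alone moves 162 to 206, while as written no sample size works. The reversal does not dispose of the alpha mismatch, which remains at equal rates (620 against 788 per arm).

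Finally, the interval's sidedness is not printed. If a one-sided 95% bound were meant, the design and analysis levels would agree, but power would still be only 35.5% at equal 67% rates and 5% as written.

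**Conclusion.** The point holds as a mismatch between the stated power and the planned analysis. The figure of 162 per arm implies one-sided 5%, whereas the planned 95% CI, taken as two-sided, is one-sided 2.5% and needs 206 per arm on the same inputs. Alpha alone accounts for a fall from 80% to about 70%, and only in the scenario where LIBS is truly 7 points better. Under equal 67% recovery the power of the planned analysis is about 25%, and under the rates as written it is 2.5%.

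This rests on the back-calculated alpha, the unpooled normal formula, 146 evaluable per arm, and the usual two-sided reading of the interval. It is not a finding of inflated type I error or of two contradictory rules in the Data analysis section.

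**What to change.** In the Data analysis section, state that non-inferiority is judged on the lower limit of the two-sided 95% CI for the recovery difference, LIBS minus CSB+, against -7 percentage points (one-sided 2.5%). State that the 5% level is two-sided and applies to the tests of difference.

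In the Sample size calculation section, state the alpha and sidedness that were used. Restate the power of 162 per arm at one-sided 2.5%, naming the assumed true rates and entering the difference in the right direction. The rates must be named because the answer is about 70%, 25% or 2.5% depending on them; printing 70% alone would replace one misleading figure with another.

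The cost is a few sentences and one recalculation. This correction asks for no additional enrolment. The downside is a less favourable stated power.

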**Methods:**

A randomized controlled non-inferiority trial will be conducted with moderately wasted children aged 6 to 59 months in Wolaita, Ethiopia. The calculated sample size is 324 (i.e. with 162 children in each of two arms, to be assigned by randomization). The daily ration will be: 100 g of LIBS plus 25.2 g of sugar with 8 ml oil in the intervention group, and 150 g of CSB+ with 16 ml of oil in the control group. These interventions will be provided for a maximum period of 12 weeks, with follow-up performed on a weekly basis. Data analysis will be done using SPSS and STATA software. Both intention-to-treat and per protocol analyses will be done. Hazard ratio and Kaplan-Meier (log rank) curves of survival analysis will be done to predict the probability of recovery rate. Logistic regression will be used to test for interactions between independent and dependent variables. Analysis of variances, t-tests, fisher’s exact test and chi-square tests will be used to assess baseline characteristics.

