### Data collection

Selected caregivers of children with MAM aged 6 to 59 months will be interviewed for collection of baseline data such as socio-demographic and economic status, dietary habits, child’s age, breastfeeding practices and history of child and maternal illness. The child’s weight will be noted using a seca weight scale to the nearest 0.1 kg. The data collectors will be sure that the scale is placed on a flat, hard, even surface and will weigh with minimal clothing.

Height will be recorded to the nearest 0.1 cm using a seca height scale for children aged 24 to 59 months. For children aged 6 to 23 months, length will be measured to the nearest 0.1 cm using a locally made wooden measuring board. Before starting height measurement, the data collectors will ensure that the height board is on level ground and the child is without shoes; the collector will kneel in order to get to the level of the child and will encourage the caregiver to help. For length, data collectors will measure the child lying down, being sure that the length board is placed on a flat and stable surface.

MUAC will be documented by non-stretchable standard United Nations Children’s Fund (UNICEF) plastic tape measures. The measurement will be taken half-way between the acromion and the olecranon processes, with the measuring tape fitting comfortably, but without making a depression in the upper arm. Weekly assessment of anthropometric measurement using MUAC will be done by the data collectors for intervention as well as control groups. On a monthly basis, data collectors will again collect anthropometrics using the MUAC, height or length board and weight scale which are identical equipment to that used at baseline. At the same time, they will observe for bilateral pitting edema. Based on the follow-up measurement of anthropometry children who developed sever acute malnutrition will be referred to SAM clinic.

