### Outcome variables

The primary outcome measure of this study will be recovery rate. ‘Recovered’ will be defined as when a child attains a MUAC ≥12.5 cm and WHZ scores ≥ − 2, without bipedal edema. The secondary outcomes are the mean recovery time and average weight gain. Children who developed SAM during the study and/or persisted as moderately malnourished at the end of the 3-month follow-up will be considered to have failed the management for MAM.

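### Kaplan-Meier is the only method named for the probability of recovery, and the handling of SAM and death is unstated; if these are censored, recovery is overstated and the arm difference can be distorted

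*Protocol article*

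**What the plan says.** All references are to the protocol article.

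- Outcome variables: "The primary outcome measure of this study will be recovery rate". The same section sets out who has failed: "Children who developed SAM during the study and/or persisted as moderately malnourished at the end of the 3-month follow-up will be considered to have failed".
- Data collection: on the follow-up measurements, "children who developed sever acute malnutrition will be referred to SAM clinic".
- Data analysis: "The probability of recovery rate will be predicted in Kaplan-Meier (log rank) curves of survival analysis". The Methods part of the Abstract names the same approach: "Hazard ratio and Kaplan-Meier (log rank) curves of survival analysis will be done to predict the probability of recovery rate".
- Data analysis, on the per-protocol set: it will "include children discharged as cured, died or non-cured". The intention-to-treat set takes all enrolled children.
- Sample size calculation: the 7% margin is absolute and is set on response percentages, 60% for LIBS and 67% for CSB+.

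The other methods named have other purposes: logistic regression for interactions, and t-tests, ANOVA and chi-square (with Fisher's exact test in the Abstract) for baseline characteristics. No competing-risk method and no censoring rule for SAM or death is given.

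**The concern.** When recovery is the event, a child who develops SAM or dies before recovering has met a competing event. The usual Kaplan-Meier set-up has one event and censors everyone else when they leave. Censoring a child at SAM referral or death amounts to assuming that the child would have gone on to recover at the same rate as the children still under follow-up. For SAM this does not fit the protocol's own definition of failure, and for death it is impossible.

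The result is that 1 minus Kaplan-Meier exceeds the share of children who recovered, and does so more in an arm with more SAM or death. In a non-inferiority trial this matters most if the new food does worse because more children deteriorate on it: those failures would drop out of the risk set instead of counting against it.

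**Working it through.** **Inputs.** Recovery of 67% (CSB+) and 60% (LIBS) and the 7-point margin come from Sample size calculation. They are used here only to represent a LIBS arm lying exactly at the margin. The 12-week horizon comes from the Abstract. The documents give no SAM or death rates, so these are assumptions and a range is shown. The plan has no figure of its own on this point to reproduce.

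**Formula.** Let R be the true share recovered by week 12 and C the share with SAM or death before recovery. With constant cause-specific hazards over 12 weeks:

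- total cumulative hazard L = -ln(1 - R - C)
- recovery part h = L × R/(R + C)
- 1 minus Kaplan-Meier with SAM/death censored = 1 - exp(-h)

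Example, R = 0.67 and C = 0.05: L = -ln(0.28) = 1.2730; h = 1.2730 × 0.67/0.72 = 1.1846; 1 - exp(-1.1846) = 0.6941.

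**Step 1: each arm alone.**

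| True recovery | SAM/death (assumed) | L | h | 1 minus KM | Excess, points |
|---|---|---|---|---|---|
| 67% | 2% | 1.1712 | 1.1372 | 67.9% | 0.9 |
| 67% | 5% | 1.2730 | 1.1846 | 69.4% | 2.4 |
| 67% | 10% | 1.4697 | 1.2788 | 72.2% | 5.2 |
| 60% | 2% | 0.9676 | 0.9364 | 60.8% | 0.8 |
| 60% | 5% | 1.0498 | 0.9691 | 62.1% | 2.1 |
| 60% | 10% | 1.2040 | 1.0320 | 64.4% | 4.4 |
| 60% | 15% | 1.3863 | 1.1090 | 67.0% | 7.0 |

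**Step 2: the difference, LIBS minus CSB+, when the truth is -7.0 points** (from unrounded values).

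| SAM/death, LIBS v CSB+ | Kaplan-Meier difference |
|---|---|
| 2% v 2% | -7.1 |
| 5% v 5% | -7.4 |
| 10% v 10% | -7.8 |
| 5% v 2% | -5.9 |
| 10% v 5% | -5.0 |
| 15% v 5% | -2.4 |

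With equal rates the gap widens slightly, against LIBS. It narrows only when LIBS has sufficiently more SAM or death.

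**Step 3: what this would do to a margin test, if the test used Kaplan-Meier.** Simulation with weekly visits, 146 evaluable children per arm (162 × 0.9 = 145.8), 4,000 replicates, and the lower limit of the two-sided 95% CI compared with -7. LIBS is truly at the margin and CSB+ has 5% SAM/death.

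| SAM/death on LIBS | False non-inferiority, Kaplan-Meier | False non-inferiority, simple proportions |
|---|---|---|
| 5% | 2.4% | 2.8% |
| 10% | 5.2% | 2.6% |
| 15% | 12.1% | 2.9% |

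**Step 4: the alternative handling.** If a child with SAM or who dies stays in the risk set as unrecovered to week 12, and no child is otherwise lost, Kaplan-Meier at week 12 is simply the number recovered divided by the number randomised. The bias from this source is then zero. Cumulative incidence gives the same value: a true 67% stays 67%.

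**The case against.** A reader might infer that the plan commits to censoring these children, and that it will therefore hide an inferior LIBS arm. The documents do not support that, for four reasons.

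- No censoring rule is stated. Holding SAM and death as unrecovered to week 12 is compatible with the text. The failure definition, and the retention of deaths in the per-protocol set, lean that way. The referral sentence does not say that follow-up ends.
- Nothing ties the 7-point decision to the Kaplan-Meier curves. The margin is set on absolute percentages, and the 95% CI appears in the sentence on the two analysis sets.
- The direction is not fixed. Equal rates bias the difference slightly against LIBS.
- The size depends on rates that the documents do not give. At 2% the overstatement is 0.9 points or less in the cases above.

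All four stand. It can also be said that a condensed article may leave censoring rules to a fuller document, and that log-rank and a hazard ratio are sound for comparing time to recovery, which is a secondary outcome. Both are fair.

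They do not dispose of the point. Kaplan-Meier is the only method the article names for the probability of recovery, and no comparison of week-12 proportions is named beside it. Belonging to an analysis set does not settle the matter either: a child can be in the intention-to-treat set and still be censored within it. Used in its conventional form, the named method conflicts with the article's definition of failure, and an estimator that agrees with that definition costs nothing.

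**Conclusion.** The concern holds conditionally. If SAM and death are censored, recovery is overstated in each arm, by about 1 point at a 2% rate and about 5 points at 10% for a true 67%. The between-arm difference is distorted when the rates differ. At 15% v 5% most of a true 7-point deficit disappears: 7.0 - 2.4 = 4.6 points.

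Masking an inferior LIBS arm needs three things together: censoring at exit, sufficiently more SAM or death on LIBS, and a margin judged on the Kaplan-Meier estimate. The documents establish none of the three, so this is a change that should be made, not a demonstrated error in the non-inferiority test. All sizes rest on constant hazards and assumed SAM/death rates.

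**What to change.** In Data analysis, and to match in the Abstract:

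1. Estimate the probability of recovery by its cumulative incidence (Aalen-Johansen), with SAM and death as competing events. Keeping those children as unrecovered to week 12 serves the same purpose, and is identical when no child is otherwise lost.
2. State that the 7-point margin is judged on the week-12 difference in recovery, LIBS minus CSB+, with its 95% CI, in both the intention-to-treat and per-protocol sets.
3. Keep the log-rank test and hazard ratio as supportive analyses of time to recovery.

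This changes wording only. It needs no new data, and STATA, already named in the plan, can run it. The one downside is that the reported recovery rates may be slightly lower than a conventional Kaplan-Meier analysis would show.

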### Aim of the study

The objective of this study is to evaluate if LIBS is as effective as standard corn-soya blend plus in treating MAM among children aged 6 to 59 months.

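### The one stated use of the 95% confidence interval is a significance reading, and no planned analysis is tied to the 7-point absolute non-inferiority margin

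*Protocol article*

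**What the plan says.** The margin appears in two places. The Hypothesis section sets non-inferiority of the recovery rate "within 12 weeks (with a 7% margin of non-inferiority"). The Sample size calculation section fixes the scale, "with the non-inferiority criterion set to be an absolute value of 7" percent, and assumes that "the expected percentage response in an experimental group is 60% and in a control group is 67" percent. The Outcome variables section makes recovery, a yes/no status for each child, the primary outcome. The Aim is worded more loosely: to "evaluate if LIBS is as effective as standard corn-soya blend plus in treating MAM".

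The Data analysis section states how inference will be made. It says "Statistical significance is set at 5% for all analyses", without sidedness. It then refers to recommendations for equivalence and non-inferiority trials, plans both intention-to-treat (ITT) and per-protocol (PP) analyses, and ends the same sentence with "the 95% CI will be used to infer whichever variances are significant". The methods named are Kaplan-Meier with log-rank, the hazard ratio, and logistic regression, the last for interactions only. The differences between groups to be computed concern recovery time, MUAC and WHZ. The abstract's Methods paragraph is similar: "Hazard ratio and Kaplan-Meier (log rank) curves of survival analysis will be done to predict the probability of recovery rate". The 7-point margin appears in neither of these two passages.

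**The concern.** A non-inferiority hypothesis on an absolute margin is tested by comparing one confidence limit, for the difference in recovery proportions, with -7 points. The article instead gives the interval a different job, which is to show what is significant. An interval that includes zero can still include deficits far beyond 7 points, so the stated reading leaves the hypothesis unanswered.

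The scale is a second gap. A log-rank p-value has no margin. A hazard ratio could be set against an absolute 7-point margin only through a conversion, and the article states none.

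At stake is the trial's main conclusion, which the Discussion intends for policymakers. With a sample of this size, a non-significant difference is likely even when LIBS is worse by the whole margin or more.

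**Working it through.** **Inputs.** From the Sample size calculation section: CSB+ 67%, LIBS 60%, margin 7 points absolute, 162 per arm including 10% withdrawal, 80% power. Evaluable number after 10% loss: 162 × 0.9 = 145.8, about 146 per arm. Assumptions: Wald intervals, and a two-sided 95% interval (one-sided 2.5%), because the article does not state sidedness.

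**The plan's own figure.** The usual formula is n = [p1(1-p1) + p2(1-p2)] × (z_alpha + z_power)² / (margin - expected deficit)². With the stated inputs the denominator is (0.07 - 0.07)² = 0, so no finite n exists. Among the variants tried, 162 appears only if LIBS is taken as 7 points better, at one-sided 5%: 0.4611 × (1.645 + 0.842)² / 0.14² = 145.4, and 145.4 / 0.9 = 161.6. That is a separate sample-size matter. It is relevant here because it means the documents do not settle the alpha.

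**What a significance reading would let through.** SE = √[(0.67 × 0.33 + 0.60 × 0.40) / n] = √(0.4611 / n).
- n = 162: SE = 0.0534 and 0.07 / SE = 1.31. P(not significant) = Φ(1.96 - 1.31) - Φ(-1.96 - 1.31) = 0.741.
- n = 146: SE = 0.0562 and 0.07 / SE = 1.246. P(not significant) = 0.762.
- Margin rule (lower 95% limit above -7 points) at the same true rates: 0.025 for either n. With one-sided 5% it is 0.05.

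At a true deficit of 10 points (57% against 67%), P(not significant) is 0.538 (n = 162) or 0.575 (n = 146), while the margin rule passes 0.006. At 12 points (55% against 67%) with n = 146, SE = 0.0567 and P(not significant) is 0.44.

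**One possible result.** Suppose 98/146 recover on CSB+ (67.1%) and 82/146 on LIBS (56.2%). The difference is -11.0 points, 95% CI -22.0 to +0.1. It is not significant, yet it plainly fails the margin.

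**Scale.** Under proportional hazards (an assumption), 60% against 67% by week 12 corresponds to a recovery hazard ratio of ln(0.40) / ln(0.33) = 0.83. No such value is given as a margin.

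**What the margin test can do with this sample.** At equal recovery of 67%, SE = 0.0522 (n = 162) or 0.0550 (n = 146). Power = Φ(0.07 / SE - 1.96) = 0.268 or 0.246. At one-sided 5% it is 0.380 or 0.355. For 80% power at one-sided 2.5%: 0.4422 × (1.960 + 0.842)² / 0.07² = 708.3, so 709 evaluable per arm, or 709 / 0.9 = 788 with withdrawal.

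**The case against.** The strongest defence is that the sentence containing the interval rule opens by following non-inferiority recommendations and plans both ITT and PP. Its ending is awkwardly worded. Read with the Hypothesis and Sample size sections, a comparison with the margin may well have been intended. An article can also leave the formal decision rule to a fuller document. This stands as evidence of intent. It does not remove the point, because the article is not silent: it states what the interval is for, and that use does not answer its own hypothesis.

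A reader might infer three stronger things that the document does not support.
- **That the protocol will declare LIBS as effective when p exceeds 0.05.** No sentence says so. The loose wording of the Aim makes that reading foreseeable, but the 74% to 76% figures are the cost of such a reading and not the error rate of a stated rule.
- **That every planned method tests zero difference between arms.** Logistic regression is planned only for interactions. Kaplan-Meier curves estimate cumulative recovery on the margin's own absolute scale. A confidence interval is not in itself a test of zero.
- **That the trial cannot test its hypothesis.** The outcome, arms, analysis sets, interval level and margin are all present. What is missing is the statement that links them.

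The 2.5% benchmark also rests on an assumption about sidedness.

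**Conclusion.** The point holds in this form: the only stated use of the confidence interval is a significance reading, no analysis names the difference in recovery proportions, and nothing in the Data analysis section refers to the 7-point absolute margin. Followed literally, the section would not test the stated hypothesis. This is a wrong statement about the primary inference and should be corrected before analysis.

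The size is conditional. If non-significance were taken as success, a product truly worse by the full margin would pass about three times in four, against one time in forty under the margin rule. This rests on the protocol's 60% and 67%, Wald intervals, 146 to 162 children per arm, and a two-sided 95% interval.

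**What to change.** Replace the confidence-interval sentence with one primary analysis:
- Estimate the difference in the proportion recovered by week 12, LIBS minus CSB+, with a two-sided 95% confidence interval.
- Declare non-inferiority only if the lower limit is above -7 percentage points in both the ITT and the PP analysis.
- State the one-sided alpha that this implies (2.5%), and use the same alpha in the sample size calculation.
- Label the log-rank test and hazard ratio as supportive.
- State that a non-significant difference is not evidence of non-inferiority.

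Adjustment for baseline MUAC, WHZ and age is optional and is not needed to cure the defect.

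The change is to wording only and needs no new data. It does expose a limit that should be disclosed. With CSB+ recovery near 67%, LIBS would have to be observed about 3 points better (114 against 109 of 162) to 4 points better (104 against 98 of 146) to meet the margin, and power at equal recovery is only about 25% to 27%. The new wording repairs the inference. It does not repair the sample size, which needs its own correction.
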